### Pilot study design

This multisite study employs a parallel-arm randomized controlled trial design with participants allocated to library-facilitated telehealth visits for buprenorphine treatment (BBB intervention) or standard-of-care clinic-based or telephone visits (control). Participants are interviewed before randomization (baseline) and surveyed again at 1-, 2-, 4-, 8-, and 12-weeks (follow-up) to assess participant characteristics and study outcomes.

The study staff also conducts weekly urine drug screenings in the libraries with participants in both study arms to assess buprenorphine uptake and potential continued use of other drugs including fentanyl and other opioids. However, these additional urine drug screening and weekly follow ups at the library are not part of the usual clinic care or telehealth treatment procedures; instead, the clinic already requires in-person urinary drug screenings. Therefore, the additional library-based drug screenings occur to promote study engagement and retention in the study assessments, and to track outcomes without sole reliance on clinic record data. We also collect medical record and pharmacy pick-up data (via the CURES database described below) as part of the study design. Although these procedures are carefully determined to ensure rigor in the evaluation design, participating in these procedures is not a requirement for the library telehealth intervention itself. Participants can continue to use library telehealth without the need for weekly drug screenings in the library upon completion of the study.

Institutional Review Boards at San Diego State University and the University of California San Diego approved this study.

### Study setting

As part of the randomization plan, the pilot study begins with the San Diego Central Library, a nine-floor public library in downtown San Diego (a high school occupies two floors).

The library has multiple conference rooms and study rooms the public can reserve. The researcher coordinates conference and study room reservations with the library for the three days of the week where the study staff meets with the participants across the two libraries.

Halfway through the targeted recruitment number of 20 participants, we will begin using a second public library site, the Mission Valley Branch Library, to recruit and provide telehealth for this study. The Mission Valley branch allows us to test the feasibility and acceptability of library-facilitated telehealth in a different indoor/outdoor library setting. The branch is smaller and less central than the downtown Central library location. It is also next to public transportation (trolley, a metropolitan commuter train) and the San Diego riverbed, where many persons experiencing homelessness have camped. Like the downtown Central library, drug overdoses have been observed at the Mission Valley branch, making it a second ideal location different enough to demonstrate feasibility and acceptability in different types of library settings.

Before this study, Father Joe’s Villages - Village Health Center, a federally qualified healthcare center (FQHC), already implemented a protocol for free, same-day medication for opioid use treatment. “Same day” means patients can have walk-in appointments (open daily on weekdays) to receive a prescription for buprenorphine from FJV Health Center which they then need to take to a pharmacy to pick-up the medication. Same-day appointment reduces barriers for unhoused patients who may otherwise need to wait for weeks before getting a prescription for buprenorphine at other local medical providers. The availability of this service is one of the reasons we sought to partner with this FQHC for the present research.

However, FJV’s tele-buprenorphine program is not well known, has limited access, and has never been tested with public libraries. The health center is connected to St. Vincent de Paul Village (Father Joe’s Villages) with comprehensive housing and food services in a downtown San Diego location where individuals experiencing homelessness congregate. It is located 0.4 miles from the downtown Central Library and 7.6 miles from the Mission Valley Library.

### Eligibility criteria

Individuals are eligible for this study if they meet the following criteria: (1) reside in San Diego County, California; (2) currently experiencing homelessness by living in a shelter, on the streets, in a car, staying with friends or family, in temporarily rented spaces (e.g., motel), abandoned building, in a tent, or otherwise unstably housed (e.g., evicted during the past month); 3) self-report deliberate use of opioids (urinary drug screening confirmation of opioid use is not required for enrollment, though it is conducted at both the library and clinic sites) within the last three months or as determined eligible for buprenorphine by the medical provider at the clinic (i.e., individuals are not eligible if they only report unintentional use of opioids, for example when other drugs used are found to be adulterated with fentanyl); 4) not currently receiving medications for opioid use disorder (such as methadone, buprenorphine, naltrexone) from another medical provider, and 5) express the desire to quit or reduce opioid use by taking buprenorphine.

### Screening and enrollment

Participants are recruited via flyers posted at reference desks and kiosks/bulletin boards at the San Diego Central and Mission Valley libraries. Non-library personnel are not allowed to approach patrons inside the library to respect their privacy. Therefore, in-person encounters within the libraries occur only when a patron approaches the research staff. The research staff sit in reserved library conference rooms. At the Mission Valley library, tables with study information are set up outside and inside the entrance to advertise the study. At the downtown Central Library, a librarian can occasionally introduce the research study over the public announcement system to refer patrons. Social work student interns formally working at the library can also refer patrons who see them for other needs. In addition, patrons may approach the library front desk or security to inquire about the study after seeing a flier or if they hear about the study from others.

Trained research staff also prescreen interested individuals for enrollment in the study during outreach outside the perimeters of the library. Recruitment around the perimeter of the libraries is sometimes necessary to spread the word about the research study. Further, because the Mission Valley library’s location is not as central in a commercial district, study staff can recruit participants in the immediate areas of the two metropolitan transit system trolley stops closest to the Mission Valley library and along trails above the San Diego riverbed where many unhoused individuals camp.

Unstably housed individuals who express an interest in obtaining buprenorphine to treat their current opioid use are invited to a reserved public library room for screening. In-person screenings are then conducted by research staff using a computer-assisted questionnaire to assess eligibility. The researchers obtain written informed consent from the participants to access their FJV Health Center medical record data about their medical appointment adherence for opioid use disorder and drug screenings on-site. Participants also consent to researchers searching CURES (Controlled Substance Utilization Review and Evaluation System), a state-level database of dispensed controlled substance prescriptions, allowing researchers to confirm whether participants picked up their controlled medications from the pharmacy. Participants indicate their preferred language for communication (English or Spanish). Researchers fluent in the selected language then review the corresponding consent form, also in their preferred language, with the participants.

For both the library-facilitated telehealth and control arms of the study, study enrollment is initiated by the study staff; enrollment is completed when the participant attends their first medical buprenorphine appointment in-person at the FJV Health Center and a medical provider confirms their eligibility for buprenorphine. Participants travel by foot from the downtown library (10-minute walk) or by trolley/bus from the Mission Valley Library to FJV Health Center. Participants receive transportation passes throughout the study. FJV prefers patrons attend the first clinic visit in-person for closer screening of buprenorphine eligibility. The study will track the number of patrons who initiate enrollment but do not make it to FJV to complete their enrollment.

### Randomization and intake

After confirmation of buprenorphine eligibility from a FJV Health Center buprenorphine provider, study staff complete study enrollment and randomize participants into one of two study arms. Both library telehealth and control group participants then complete interviewer-administered surveys and follow-up interviews over the 12 weeks of the study conducted at the libraries. Study staff contact all patrons in both study arms, including those who missed appointments or do not return to participate in the research study at the libraries, to help reconnect them to the research study.

### Study materials and incentives

For each baseline and follow-up visit for library-facilitated telehealth and control arms, all participants completing assessments with the library researcher staff receive $20 cash (gift card optional), transportation day passes per library visit with the researcher, and snacks/drinks.

### Intervention condition

In the intervention group, participants are scheduled for regular appointments at the FJV Health Center, which they attend via telehealth at the library. However, they can also access telehealth with FJV Health Center at unscheduled times. Unscheduled drop-in appointments is a standard available option for FJV Health Center patients and can be extended to library telehealth. The ability of unhoused participants to keep their regular buprenorphine appointments, whether in-person or by library telehealth, is a process measure for the study.

In some situations, participants can be interviewed outside of the library, if a room is not available in the library or the participant has too many belongings to bring inside the library.

Efforts are made to keep appointments private in locations not within hearing distance of others. The libraries have a computer tablet on a telehealth floor stand in a private study room for this study. The libraries make the computer tablet available on a heavy platform (to prevent theft) that can be placed in a library study room. The tablet is an alternative that removes barriers for patrons without ID cards who would otherwise need an ID card to check out library laptops.

FJV medical providers follow standard of care practice (whether in-person visit or over telehealth) to provide medication adherence counseling, medication education (e.g., how to take buprenorphine), information about what to expect, appointments, and treatment goals (e.g., relapse prevention, health/mental health referrals). Researchers help make follow-up appointments with the FJV Health Center for both the control and telehealth library groups, and research or library staff can also assist patrons with logging on to their telehealth appointments.

As part of usual care for participants in both study arms, participants are still expected to attend the FJV Health Center in-person when asked to do a follow-up urinary drug assessment at the clinic, despite participating in the drug screenings weekly at the library. Participants in the library-facilitated telehealth arm are not forced to use the telehealth option solely; they can still attend in-person medical visits (provide clinic urine samples), Alcohol and Drug (AOD) counselor visits, and support groups at the clinic. Therefore, the continued in-person visits to the clinic and uptake of library telehealth is another process measure. As described below, the control group is only offered library-facilitated telehealth once they complete their 12-week study participation.

### Control condition

Like the library-facilitated telehealth condition, participants in the control condition receive the same medical treatment in phases based on an individual case basis, case management referrals by research staff, research incentives, and face-to-face follow-ups by the researchers at the library. The only difference between the study arms is that control participants are not offered library-facilitated video sessions during the 12-week participation in the study.

However, after completing the 12 weeks in the study, control participants have the option of library-facilitated telehealth.

### Outcome ascertainment and post-intervention assessments

Intervention outcomes determine the feasibility, acceptability, and retention in the library telehealth intervention at baseline, 1-,2-,4-,8-, and 12-weeks on (1) weekly urine drug screenings (for buprenorphine uptake and other drugs); (2) buprenorphine prescription pick-ups; (3) clinic visits; and (4) self-reported measures (e.g., substance use, mental health, quality of life). (see Table 1).

**Table 1 Tab1:** BBB intervention targets, strategies, and specific activities

**Intervention targets**	**Intervention strategies**	**Examples of specific activities**	**Data Collection Format**
Feasibility and acceptability of library telehealth for buprenorphine uptake (pharmacy pickup, taking prescription one or more times) and adherence (more than one buprenorphine positive screen or taking buprenorphine for 8 + weeks)	Participants use library telehealth. Data are used to assess participant satisfaction (in exit interviews) and identify areas for improvement.	All participants in the library-facilitated telehealth and control groups complete a post-treatment satisfaction survey regardless of whether they sustained in treatment. At the end of the participants’ 12-week participation in the study, research staff interview participants about their experience with library telehealth and the acceptability of BBB study participation. The investigators survey medical providers and library staff involved in the study about their experiences with the study protocol.	Surveys and interviews, delivered by a researcher not involved in their care. Satisfaction measures are embedded in the follow up exit survey and interview using specific items generated by the study about the telehealth and study experiences.
Awareness of buprenorphine availability	Basic buprenorphine education, increase in knowledge of service providers.	General information on buprenorphine availability at Father Joe’s Villages and in the San Diego region.	Personalized discussion, resource list delivered by researchers and library social work interns.
Apprehension toward buprenorphine*	Basic buprenorphine education, increase knowledge of health.	General background on buprenorphine treatment (e.g., targeting of opioids). Facts about buprenorphine. Buprenorphine treatment information.	Brief educational information sheets delivered by researchers/library social work interns and FJV Health Center staff.
Limited MOUD treatment skills	Problem-solving	Identifying challenges relevant to individuals in continuing through treatment (e.g., personal identification for pharmacy, contact information for reminders).	Personalized discussion to address barriers delivered by researchers/library social work interns and FJV Health Center staff.
Limited telehealth behavioral skills	Modeling	Modeling process of logging in to the telehealth system. Education on what medical professionals to expect and when (e.g., nurse followed by the doctor).	Demonstration delivered by researchers/library social work interns.

***Buprenorphine Apprehension.** Though individuals want to try buprenorphine to help them treat their opioid use, some fear of possible significant side effects, such as precipitated withdrawals. Others perceive buprenorphine would not work for them or they do not know what it is

### Data collection

#### Baseline and longitudinal assessments/measures

Following a FJV Health Center physician’s buprenorphine prescription, research staff track the participants’ buprenorphine medication uptake (pharmacy pickup, taking prescription one or more times during the first two weeks in the study), adherence (more than one buprenorphine positive screen), and medical appointment keeping through urinary drug screenings, interviews conducted at public libraries, and medical record data. All participants are invited to return to the library weekly for urinary drug screenings and to complete follow-up survey assessments at weeks 1, 2, 4, 8, and 12. Baseline and follow-up assessments are conducted in reserved library study rooms or conference rooms.

The 60-minute baseline survey captures the following domains: sociodemographic, behavioral, social supports, telehealth utilization and comfort, library usage, substance use behaviors, overdose experiences, and treatment history, along with the biomarker and medical record data collection (see Table 2). The content of the follow-up surveys is the same as the baseline surveys except that participant history and demographics are removed. The follow-up survey is shorter (30 min), retaining questions surrounding buprenorphine uptake, healthcare utilization, and barriers and facilitators to use. Follow-up questions also ask participants to recall experiences since their last visit with the research team in the library, particularly to determine the feasibility and acceptability of the library telehealth intervention; ease and understanding of being in the randomized controlled trial; experiences following up with the medical provider whether in-person or by telehealth; and their experiences with picking up and taking the buprenorphine medication.

Urinary drug assessments at the library are not part of the intervention, but rather part of the research assessment procedures and to better track participants over time (a strategy for reducing loss to follow up). Urinary drug assessments for buprenorphine are still required in-person at the clinic as the routine medical procedures for both arms of the study, a standard procedure even during the COVID-19 pandemic at FJV Health Center. The urinary strips at the library are dipsticks used to assess for buprenorphine, fentanyl, and other drugs to assess for the primary outcome of the study (buprenorphine uptake and adherence) and secondary outcome (reduction of fentanyl and other drugs). The participants use library bathroom facilities to collect their weekly self-administered urinary drug screening tests. Patrons take the urinary drug test strips (for buprenorphine, fentanyl, and other drugs) and a plastic cup to the library bathrooms and return the test strips in a clear hazard bag for the study staff to record in a de-identified log. After each visit with research staff, participants receive 20 dollars cash and a Metro Transit System pass(es) as reimbursement for their time and travel needs to and from their clinic or library appointments. As noted above, these urinary drug assessments in the library and incentives/compensation are not required or offered for the telehealth intervention in the library after the study ends. Only the library telehealth would still be available.

We anticipate that many participants do not have a cellular phone or reliable phone access as phones are often lost, stolen, or run out of minutes due to the individual’s economic vulnerabilities, which exposes them to theft from other individuals, lack of income to pay the bill, and “sweeps” or forcible displacement from law enforcement. For follow-ups, the research staff obtain alternate phone numbers and emails of other individuals who can locate the participant. However, participants will be provided with information on the days and times the research staff are at the library and can simply show up at those designated times (two or three days per week). Researchers also keep library staff and security informed of the study location within the library and times of researcher availability to facilitate follow-up meetings with participants.

**Table 2 Tab2:** Measures

Topic/Variable	Covariate Measure	Survey instrument/measure
**Feasibility and Acceptability of the Intervention and RCT study design**	Example: You were randomly assigned to either telehealth in the library with your FJV prescribing doctor or in-person follow-ups with your FJV prescribing doctor. Which would have worked better for you and for what reasons?	Study generated (open and close ended questions) *Feasibility of the telehealth intervention*: Participant completes 1 + appointment with the buprenorphine provider via telehealth at the library. Document barriers to telehealth that arise (e.g., internet connection issues) *Acceptability of the telehealth intervention*: Qualitative interviews during the intervention and via exit interviews asking about the participants’ experiences with telehealth, as well as the library and clinic staff’s experiences with delivering the library telehealth *Feasibility of RCT to evaluate the current intervention*: Rate of enrollment (Number of participants per week and per month), Proportion of interested and eligible participants who can successfully complete enrollment in the study, Study retention (proportion of RCT-enrolled participants who complete each follow-up assessment), Proportion of RCT-enrolled participants for whom outcome data are collected.
**Primary Outcomes**		
Buprenorphine uptake and adherence	Biomarkers: urinary drug assessments at the library and clinic. Pharmacy pickups of buprenorphine Self report: “How often do you take it? What is the dosage? Are you taking it correctly (as prescribed)? If not, why?” “Did you run out of your prescription before getting a refill?” “Have you stopped taking buprenorphine?”	Study generated Uptake: the proportion of people who pick up from the pharmacy and take buprenorphine 1 or more times at initiation, i.e., during the first 2 weeks, confirmed by biomarkers (urinary drug screens at the library and clinic, pharmacy pickup data from the state’s CURES database) Adherence = more than one buprenorphine positive screen taken at the library or at the FJV Health Center, ideally for 8 + weeks.

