As a primary outcome, buprenorphine *uptake* is defined as a pharmacy pickup and taking the prescription one or more times during the study period. Buprenorphine *adherence* is indicated by more than one buprenorphine positive screens taken at the library or at FJV Health Center and ideally continuing to take buprenorphine as prescribed for eight or more weeks. The rationale for the primary outcomes, buprenorphine uptake and adherence, via weekly drug screening, is to try to capture the patterns of buprenorphine uptake and adherence among unhoused populations, a likely more isolated and neglected group when it comes to finding, starting, and adhering to buprenorphine due to being unhoused. Therefore, we measure adherence as a primary outcome with 1 + buprenorphine positive tests, ideally for 8 + weeks of 12 weeks (3 months), rather than the standard 3–12 months adherence.

In the study’s formative stages of intervention development, study staff conducted interviews and focus groups with library patrons (those experiencing homelessness or living in a shelter or treatment program), library staff (i.e., security personnel, librarians, outreach workers), general public/parents, and buprenorphine providers to get reactions to the proposed program and to inform the study design. For example, five focus groups with library patrons were conducted across four libraries in San Diego to assess the potential feasibility and acceptability of the planned intervention. The findings from these interviews and focus groups inform the design of the telehealth intervention at the libraries and the measures that can be used in a randomized controlled trial. For example, we gained insights for recruiting and screening participants for opioids (being discreet in public spaces), enrollment procedures (coordinating with medical providers), and timing of the randomization (after first buprenorphine medical provider visit). Another recommendation made is to have persons with lived experience, especially with substance use recovery and experiences with buprenorphine, on the team. Focus group participants suggested recruitment strategies such as placing flyers at specific library bulletin boards frequently visited by unhoused individuals, which many identify as providing a consistent and reliable source of community information.

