#### Sample size and planned data analyses

Our target sample size for the trial is 40 participants, although we allow for a maximum of 60 participants to account for attrition. The sample size will provide adequate precision for effect size estimates, though not statistically powered to assess efficacy on primary outcomes.

Buprenorphine uptake (the proportion who pick up and take buprenorphine at initiation, confirmed by CURES database pharmacy pickup records and urinary drug screenings) and adherence (taking buprenorphine > 1 time, ideally for 8 + weeks), medical appointment adherence (attended medical appointments for buprenorphine two or more times as confirmed by clinic medical record data) will be divided by the number prescribed and scheduled, respectively.

Adherence estimates from this study will also provide the basis for power calculations in the design of future efficacy trials. Quantitative data analysis will consist of univariate statistics to describe the entire study sample and by study arm, the prevalence of individual responses, and the prevalence of treatment uptake and adherence. We will conduct an intent-to-treat (i.e., per-randomization) analysis following CONSORT guidelines to explore potential differences between study arms on the outcomes. Specifically, we will use regression models testing each outcome separately (using the appropriate test depending on the outcome distribution, e.g., logistic regression with binary outcomes). These models will treat the intervention condition (library-facilitated telehealth intervention vs. treatment-as-usual control) as the exposure in unadjusted models.

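### Adherence can be met by two positive screens from a single dose, because library and clinic screens are pooled with no spacing rule

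*Protocol article*

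**What the plan says.** Adherence is a primary outcome alongside uptake, and the article defines it in several places:

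- Table 2, Primary Outcomes: "Adherence = more than one buprenorphine positive screen taken at the library or at the FJV Health Center, ideally for 8 + weeks".
- Methods, end of the objectives text (under Feasibility of RCT to evaluate the current intervention): "more than one buprenorphine positive screens taken at the library or at FJV Health Center". Later in the same paragraph: "we measure adherence as a primary outcome with 1 + buprenorphine positive tests, ideally for 8 + weeks of 12 weeks (3 months".
- Table 1: "adherence (more than one buprenorphine positive screen or taking buprenorphine for 8 + weeks".
- Baseline and longitudinal assessments/measures: "adherence (more than one buprenorphine positive screen", with no mention of eight weeks.
- Sample size and planned data analyses: "adherence (taking buprenorphine > 1 time, ideally for 8 + weeks".

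Two screening streams run side by side. Participants in both arms are invited to the library each week for a strip test. The clinic also asks both arms for its own in-person urine screens, "despite participating in the drug screenings weekly at the library" (Intervention condition). The frequency of clinic screens is not given. Study setting says of the clinic: "It is located 0.4 miles from the downtown Central Library". It is 7.6 miles from the Mission Valley library.

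Uptake needs a pharmacy pickup and taking the drug at least once. The analysis section says that adherence estimates will feed the power calculations of future efficacy trials.

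**The concern.** The operative criterion is a count of two positives from either place. Eight weeks is only an ideal, and in Table 1 it is an alternative to the two-screen count. No definition says that the positives must come from different days, weeks or doses.

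A participant who takes one dose, gives a clinic sample and walks to the Central Library for the weekly strip can have two positives from that dose. The rule then records adherence, but the analysis section's own meaning, taking the drug more than once, has not been shown.

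Two things are at stake. The adherence proportion may be too high, and it is an estimate that the pilot is meant to hand on. The error may also differ by arm. Control participants are seen at the clinic or by telephone, and intervention participants mainly by library telehealth. If clinic screens tend to accompany in-person visits, the arms will have different numbers of chances for a second, closely spaced positive. The weekly library contact is common to both arms but does not equalise clinic screens.

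**Working it through.** The plan attaches no rate, power or effect size to adherence, so there is no figure to reproduce. The check has two parts.

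**Reading the definitions together.** All the screen-based versions pool or do not distinguish the sites, and none has a spacing condition. The version in the Methods rationale asks for one or more positive tests. That contradicts the more-than-one rule in the same paragraph and would let a single positive suffice. Pharmacy pickup and self-report are listed in Table 2 under the joint heading of uptake and adherence, but the adherence rule uses screens only, so they do not repair it.

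**How likely one dose is to give two positives.** Inputs:

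- Weekly library screen, from the article. The first one after the dose is taken as uniform over 0 to 7 days.
- Urine stays positive for W days after one dose. This is an assumption; the documents give no window. Range 1 to 6 days.
- One clinic screen, uniform over the C days after the dose and independent of the library screen. This is an assumption; range 7, 14 or 28 days.

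For W up to 7, P(two positives) = (W/7) × (W/C). For example, with W = 4 and C = 14: (4/7) × (4/14) = 16/98 = 0.16. If the clinic and library screens fall on the same day, P = W/7.

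| W (days) | C = 7 | C = 14 | C = 28 | Same day |
|---|---|---|---|---|
| 1 | 2% | 1% | 0.5% | 14% |
| 2 | 8% | 4% | 2% | 29% |
| 4 | 33% | 16% | 8% | 57% |
| 6 | 73% | 37% | 18% | 86% |

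Simulation with 400,000 draws per setting agrees to within 0.2 percentage points.

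The C = 7 and same-day columns place the clinic screen in the seven days after the dose. If instead the dose falls at random within a study week containing one screen of each kind, a screen may precede the dose and the values are lower:

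- Independent days: [(7 − W)W² + W³/3]/343 = 7%, 20% and 31% for W = 2, 4 and 6.
- Same day: (7W − W²/2)/49 = 24%, 41% and 49%.

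**Library screens alone.** With strips exactly 7 days apart, one dose cannot give two positives for W below 7, so P = 0. The weakness comes from pooling the two places without spacing. The zero depends on exact weekly spacing. Participants may come on any of two or three staffed days a week, so library screens in consecutive weeks can be less than 7 days apart.

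**Under a rule of two positives at least 7 days apart.** P = 0 for every W below 7.

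**Weight of one misclassification.** With the target of 40 and equal arms (an assumption), each arm has 20 participants, so one misclassified participant moves that arm's proportion by 1/20 = 5 percentage points.

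**The case against.** The strongest reply is that handling several screens in one week is a derivation detail that a condensed article leaves to the full plan, and that the wording about taking the drug more than once shows what is intended. It is true that the article never says same-day duplicates count twice. But it does fix the counting rule, repeatedly and for a primary outcome, and the rule as written is met by such a pair.

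Other parts of the reply stand:

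- The size is almost wholly assumption. Neither the detection window nor the clinic frequency is given; the article says only that clinic samples are given when asked for.
- The intake visit comes before prescription and pickup, so an intake screen cannot be positive from the first study dose. A later clinic screen is needed.
- Same-day testing is easy from the Central Library but less so from Mission Valley.
- A low threshold is a reasoned choice for an unhoused population in a pilot not powered for efficacy. The point here concerns spacing and does not ask for a higher threshold.

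A reader might infer that adherence collapses into uptake. The documents do not support that. Uptake also needs a pharmacy pickup, and Table 2 and the data collection section confine it to the first two weeks. Nor is it known how many participants would take one dose, stop, and still attend both places within the window. A reader might also take the table as expected misclassification rates. Each entry is conditional on a single dose and one clinic screen, so none is a trial rate.

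**Conclusion.** The point holds as a weakness in a stated primary-outcome rule: two positives pooled over two concurrent streams, with no separation, do not establish repeated taking. For a same-day pair no particular detection window need be assumed, only that both samples are taken while the urine is still positive.

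Its size cannot be derived from the documents. Under the assumptions above, the conditional probability runs from about 0.5% (1-day window, clinic screen spread over 28 days) to about 86% (6-day window, same-day screens). The direction is upward for the adherence proportion. A difference between arms is possible but not shown, because it depends on whether clinic screens follow in-person visits, and both arms are asked for clinic samples. The correction is cheap and should be made before outcomes are derived.

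**What to change.** Count at most one positive per study week, whichever site took the sample. Define minimum adherence as positives in at least two different study weeks, at least 7 days apart, or separated by another stated gap that exceeds the strip's detection window. The gap is needed as well as the week rule, because screens at the end of one week and the start of the next can be only a few days apart.

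Use this one rule in the Methods outcome paragraph (replacing the version that asks for one or more positives), Table 1, Baseline and longitudinal assessments/measures, Table 2, and Sample size and planned data analyses. Bring the Abstract and Background into line.

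The article documents dates for library sessions. For clinic screens it mentions recording outcomes but not dates, so clinic dates should be taken from the medical record data already being collected.

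No new visit or test is needed. The cost is the extraction of clinic dates, a slightly lower adherence proportion, and a few genuine pairs 5 to 6 days apart that would not count under the 7-day gap.
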